## Interventions

### Explanation for the choice of comparators {6b}

The PD intervention group is compared with the PD control group and a healthy control (HC) group. The PD control group is composed of participants diagnosed with PD and who meet the inclusion criteria. This PD control group is instructed to maintain the participants’ prescribed medication and care documented at the time of baseline assessment including any form of deep brain stimulation, if applicable. Any deviation from what was recorded at the time of taking baseline assessments are recorded during assessments and included when analyzing the data.

The second control group, the HCs, is composed of participants who meet the HC group inclusion criteria. This group predominantly consists of healthy spouses of the PD participants and individuals who share similar demographics to the participants diagnosed with PD. Measurements from the HCs are necessary because they serve as a normal, non-pathological benchmark, which has not been recorded before with this specific demographic and type of study paradigm. Furthermore, since spouses typically have similar lifestyles as their partners the measurements taken may help reduce the uncontrollable deviations due to dietary habits, living conditions, and environmental factors. HCs are asked to continue normal routine and must report any major deviations from baseline assessment routine (e.g., new medication to treat non-neurological illnesses that may affect motor movement or major injuries like head trauma). These deviations are noted for data analysis.

The neuronal activities of generating motor movement or processing a rhythmic external cue each should separately elicit measurable neuronal activation. However, when combined, a sensorimotor integration effect occurs such that motor movement is the result of a rhythmic external cue. Thus, the use of the HC and PD controls is to examine how movement coupled with an external sensory cue (a rhythmic auditory stimulus and in this study, music with rich rhythmic contents) impacts motor synchronization and control in PD.

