### Intervention description {11a}

After the baseline measurements, participants in the intervention arm will be trained to do a rhythmic auditory synchronous finger tapping (SFT) intervention task at the hospital and asked to practice at home for a total of 25 min split between two 10-min sets with a 5-min break between the sets every day for 8 weeks. During training sessions participants must listen to the instrumental of a pre-selected well-known Chinese melody, i.e., 荷塘月色 (pinyin: “hé táng yuè sè”; English: “Moonlight over the Lotus Pond” by Phoenix Legend) whose melody duration is 259 s. This song was selected for its strong beat and familiarity to most of the participants. Participants must follow the beats of the melody and tap their right index finger simultaneously to the beats. The training session will be conducted once daily after patients have taken their medication. They are also instructed to take a video recording of themselves with their smartphones for the entire duration of the training. They may also solicit the help of their primary caregivers for the recording. This is for the purpose of monitoring protocol compliance.

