### Criteria for discontinuing or modifying allocated interventions {11b}

Participants may stop participation at any time during weeks 0–12 due to various reasons including failure to meet inclusion criteria or inability to continue at-home intervention.

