### Strategies to improve adherence to interventions {11c}

Participants’ primary caregivers are asked to monitor and, if needed, record completion of sessions using a smartphone with video and audio recording capabilities. The videos will be collected weekly either digitally through a secure cloud server or transferred from the phone if participant is available to come to the hospital on a weekly basis. Participants who do not have caregivers may be provided with a phone ring stand to help with recording themselves, if needed. In addition, a phone with video and audio recording capabilities is provided for participants who do not have one. These videos will be reviewed by a research assistant who is not involved in data collection or enrollment. For the intervention group, videos are scored separately for adherence and accuracy. Accuracy is determined by matching the time sequence of the song to that of the one used during the assessment. The HC and the control arm’s videos are scored on a binary adherence score. These scores are manually inputted into a designated spreadsheet and updated in the database weekly.

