**Fig. 1 Fig1:**
[figure not shown]
Expected trial plan. Not included in the diagram are excluded participants that may stop participation at any time during weeks 0–12 due to various reasons including failure to meet inclusion criteria or inability to continue at-home intervention. The intervention tasks are 25 min total, with two 10-min sets with a 5-min break between each set

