### Recruitment {15}

Potential participants are recruited from the First Affiliated Hospital of Dalian Medical University. Recruitment will be managed by BZ and ZL. Participants’ spouses are also invited to participate as healthy controls if they meet the inclusion criteria. We will assume a conservative estimate of 10% attrition due to various reasons such as voluntary withdrawal, illnesses during studies, and other uncontrolled factors.

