## Statistical methods

### Statistical methods for primary and secondary outcomes {20a}

Data analysis will commence after all retained recruited participants have completed their 12-week assessment.

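### Inability to continue the at-home training is written as a reason to leave the study, with no continued assessment, so outcomes can be lost mainly from one randomised arm

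*Protocol article*

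**What the plan says.** All references are to the protocol article.

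- **Criteria for discontinuing or modifying allocated interventions {11b}.** The whole section is one sentence, permissively worded, under which people are free to "stop participation at any time during weeks 0–12 due to various reasons including failure to meet inclusion criteria or inability to continue at-home intervention". It sets out reasons to leave the study and nothing about stopping the intervention alone.
- **Participant timeline {13}, Fig. 1 legend.** "Not included in the diagram are excluded participants that may stop participation at any time during weeks 0–12", with the same reasons then repeated.
- **Intervention description {11a}.** "participants in the intervention arm will be trained to do a rhythmic auditory synchronous finger tapping (SFT) intervention task" and practise it at home every day for 8 weeks.
- **Explanation for the choice of comparators {6b}.** "This PD control group is instructed to maintain the participants’ prescribed medication and care documented at the time of baseline assessment".
- **Strategies to improve adherence {11c}.** "The HC and the control arm’s videos are scored on a binary adherence score". This implies some recorded home activity outside the training arm, but its content is not described. Concealment mechanism {16b} likewise refers to at-home instructions specific to each group.
- **Recruitment {15}.** "We will assume a conservative estimate of 10% attrition due to various reasons such as voluntary withdrawal, illnesses during studies, and other uncontrolled factors". The figure is not split by arm.
- **Statistical methods {20a}.** "Data analysis will commence after all retained recruited participants have completed their 12-week assessment".
- **Methods to handle non-adherence and missing data {20c}.** Missing values, and data collected outside the protocol, are dropped from the analysis.
- **Additional consent provisions {26b}.** The consent form asks whether data may be used after withdrawal. It does not provide for further measurement.

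**The concern.** Stopping a treatment and leaving a trial are different events. Section {11b} is headed for the first and describes only the second. A participant who finds daily tapping unmanageable is offered one route, which is to leave. The outcomes in section {12} are changes from baseline judged at weeks 4, 8 and 12, so whoever leaves has no values from that point on.

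The tapping is the intervention arm's task, so this reason for leaving arises mainly there. A comparable control participant has no such task to give up and goes on being measured. If those who cannot keep up are the ones whose motor or cognitive function is declining, the training-arm mean is taken over people who could sustain the exercise. Success in section {12} is largely defined as scores kept or improved, so losing decliners from one arm can resemble success.

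The rule for removing data in {20c} is a separate problem. Correcting {20c} alone would leave an as-randomised analysis with no values for these people after they stop. The Discussion also suggests the exercise might be prescribed in practice, so the number who could not continue is a result worth reporting.

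**Working it through.** **1. The passages side by side.**

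| Question | Where | Answer |
|---|---|---|
| Is inability to train a listed reason to leave? | {11b}, Fig. 1 legend | Yes, permissively worded |
| Are those people in the expected trial plan? | Fig. 1 legend | No, they are classed as excluded |
| Who does the training? | {11a} | The intervention arm |
| Is any home task implied elsewhere? | {11c}, {16b} | Yes, content not described |
| Is assessment after stopping training provided for? | {11b}, {18b}, {26b} | No statement. {18b} is a scheduling reminder and {26b} covers use of data only |
| Whose data does the analysis wait for? | {20a} | Retained participants |

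**2. The plan's own figure.** Sample size {14} gives 70 per group, 210 in all, with 10% attrition, so 70 × 0.9 = 63 evaluable per arm. No difference or SD is stated, so 70 cannot be reproduced from the plan's inputs. With an *assumed* standardised difference of 0.5, two-sided 0.05 and 80% power, n = 63 per arm and 63/0.9 = 70. I use 0.5 SD below only as a yardstick.

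**3. Bias if the least able leave.** Assumptions, none from the documents:
- there is no true effect;
- the 7 of 70 lost from the training arm (10%) are those with the lowest latent ability to continue;
- the 7 lost from control are random;
- ability and outcome have correlation ρ.

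Removing the lowest 10% of a standard normal raises the mean of the rest by φ(1.2816)/0.9 = 0.195 SD, so bias = 0.195 × ρ. A simulation of 6,000 trials per setting, with a two-sample t test, gives:

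| ρ | 0.195 × ρ | Simulated bias (SD) | False finding of benefit (nominal 2.5%) |
|---|---|---|---|
| 0.3 | 0.059 | 0.06 | 5.4% |
| 0.5 | 0.098 | 0.10 | 8.5% |
| 0.7 | 0.137 | 0.13 | 12.2% |
| 1.0 | 0.195 | 0.19 | 21.4% |

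The closed form is a large-sample value, so small differences from the simulation are expected. With 10 of 70 lost in this way and ρ = 0.5, the results are 0.13 SD and 11.7%.

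**4. A second model as a check.** Let f be the share of the training arm lost and g the completers' mean outcome minus the leavers', in SD. Control loss is taken as unrelated to outcome. Then bias = f × g, and two-sided type I error follows from dividing it by √(1/n₁ + 1/n₂).

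| Lost from training arm | n₁ v n₂ | g | Bias (SD) | Two-sided type I error |
|---|---|---|---|---|
| 10% | 63 v 70 | 0.5 | 0.05 | 0.060 |
| 10% | 63 v 70 | 1.0 | 0.10 | 0.089 |
| 20% | 56 v 70 | 0.5 | 0.10 | 0.086 |
| 20% | 56 v 70 | 1.0 | 0.20 | 0.200 |
| either | | 0 | 0 | 0.050 |
| 10% to 20% | | −0.5 | −0.05 to −0.10 | 0.060 to 0.086 |

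The 20% rows put all 14 of the 140 expected losses from the Parkinson's arms (10%) into the training arm. Against the assumed 0.5 SD effect, 0.05 to 0.20 SD is 10% to 40%. The last two rows show that the sign depends on g, which the documents do not give.

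**The case against.** **Permission, not a rule.** Section {11b} says participants may stop, which matches the right to withdraw at any time. A reader might infer that anyone who stops training must leave. The text does not say so. What stands is that leaving is the only route described, and the Fig. 1 legend counts those who take it as excluded.

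**Not every measurement is lost.** A reader might infer that these people reach none of the follow-up visits. Stopping can occur at any time in weeks 0 to 12, so someone who stops in week 6 already has a week 4 value. Training ends at week 8, so inability to train cannot itself cause an exit after that. Only visits after the exit are lost.

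**The tie to one arm is not exclusive.** Sections {11c} and {16b} imply home activity in the control and healthy groups, and the other listed reason, failing the inclusion criteria, applies to both Parkinson's arms. The exit falls mainly, not only, on the training arm, and these sections need reconciling.

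**The direction is assumed.** In a change score, a stable deficit largely cancels, and only differential worsening biases the comparison. The simulation uses a single outcome with no baseline. Nothing shows that leavers would have less favourable HbO2 change, and HbO2 is the outcome that section {14} names for sizing the trial. A reader might infer that the result is tilted towards benefit. The documents support only that it can be.

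**The scenario is near a worst case.** Section {15} attributes the 10% to withdrawal, illness and other factors. Participants are at Hoehn and Yahr stage I to II, and the task is two 10-minute sets. This is fair, and it is why a range is shown. Nor is non-completion wholly hidden, since adherence is scored from videos each week.

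**An article condenses.** A missing operational detail would be no finding. Here, however, the article states the exit route twice, and the statement as drawn merges two events.

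**Conclusion.** The point holds in limited form, as an inexpensive improvement worth making. The article merges stopping the at-home training with leaving the study, classes those who leave as excluded and provides no assessment after training stops. Because the training is the intervention arm's task, the loss falls mainly on one side of the randomised comparison, and no later analysis can recover it.

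The size is conditional. It is about 0.06 to 0.19 SD of spurious benefit for an assumed correlation of 0.3 to 1.0, with 10% of the training arm lost from the least able and random loss in control. It is zero if leavers do not differ, and runs against the training if they do better. The documents do not establish that the bias exists, that it favours the intervention, or that it reaches HbO2.

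**What to change.** - In section {11b} and the Fig. 1 legend, separate stopping the at-home training from withdrawing from the study. The legend should not class people who only stop training as excluded.
- State that participants who stop training are still invited to whichever of the scheduled week 4, 8 and 12 assessments remain, and are analysed in their randomised arm.
- Report both kinds of stopping, by arm, in the participant flow.
- Change section {20c} so that data are not removed for non-adherence in the main comparison of the two Parkinson's arms. Without this, the values collected after stopping would be discarded again.
- Reconcile {11c} and {16b} with {6b} on what the control and healthy groups do at home.

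None of this changes when or why anyone stops the training. The cost is edits to a few sections and one legend, since the visits are already scheduled. The downside is that the estimated effect will include people who stopped training and may be smaller. Some will still decline to attend, so the loss is reduced and not abolished. For those who attend, this source of selection is removed.

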### Strategies to improve adherence to interventions {11c}

Participants’ primary caregivers are asked to monitor and, if needed, record completion of sessions using a smartphone with video and audio recording capabilities. The videos will be collected weekly either digitally through a secure cloud server or transferred from the phone if participant is available to come to the hospital on a weekly basis. Participants who do not have caregivers may be provided with a phone ring stand to help with recording themselves, if needed. In addition, a phone with video and audio recording capabilities is provided for participants who do not have one. These videos will be reviewed by a research assistant who is not involved in data collection or enrollment. For the intervention group, videos are scored separately for adherence and accuracy. Accuracy is determined by matching the time sequence of the song to that of the one used during the assessment. The HC and the control arm’s videos are scored on a binary adherence score. These scores are manually inputted into a designated spreadsheet and updated in the database weekly.

### Relevant concomitant care permitted or prohibited during the trial {11d}

Participants must maintain a stable dosing of anti-PD or deep-brain stimulation (DBS) treatment throughout the duration of the study, if applicable to the individual.

### Provisions for post-trial care {30}

Not applicable to study; no harm is anticipated from this study as the equipment used has minimal risks.

### Outcomes {12}

The primary outcome measurements of this study are the following:
Improvement or preservation of SFT and continuous finger tapping (CFT) performances from baseline measurements for intervention group.Preserved or improved the Unified Parkinson’s Disease Rating Scale (UPDRS) scores from baselines measurements for intervention group in comparison to control arm.Reduced HbO_2_ levels in prefrontal cortex from baseline measurements for intervention group. Preserved or improved n-back task scores from baseline measurements for intervention group in comparison to control arm.Preserved or improved Montreal Cognitive Assessment (MoCA) scores from baseline measurements for intervention group in comparison to control arm.

Secondary outcome measurements of the study include:
Preserved motor control performances, UPDRS scores, HbO_2_ levels, n-back task scores and MoCA scores from baseline measurements in healthy control group.Preserved or aggravated motor control performances, UPDRS scores, HbO_2_ levels, n-back task scores, and MoCA scores from baseline measurements in PD control group.

These outcomes are determined by analyzing the differences between participants’ pre-, 4-week (during), 8-week (post), and 12-week (retention), neuroimaging, neurophysiological, and SFT performance scores as well as compared with the data from the control arms. Individual and grouped averaged measurements are examined.

Music-based therapies often report beneficial and positive results; however, little is known about how music improves neuronal activity and connectivity in individuals with neurological disease. The primary outcome measurements of this protocol: SFT and CFT performances, HbO2, UPDRS scores, n-back, and MoCA scores act as assessments to quantify the effects of a music-based synchronous finger tapping training in individuals with PD. The trial’s outcomes may be used to enhance current clinical care of patients with PD by supplementing or augmenting current PD treatments with music-based exercises. There are currently no anticipated harmful outcomes because the use of fNIRS has been shown to be clinically safe and feasible. Consequently, this study was determined to be a low-risk intervention by the participating hospital’s Ethics Committee and the Steering Committee.

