## Objectives {7}

This study’s primary objective is to investigate how external auditory stimuli coupled with motor movement affect motor synchronization and control in patients with PD to further understand how movement based music therapies or other forms of trained auditory cued movement impact the neural activity in key cortical timing brain regions. To achieve this, we propose the following objectives:
Determine neuronal activation and motor control performance in normal, healthy controls (HC) whose lifestyles and demographic are like those of the PD intervention group and PD control group.Implement an 8-week intervention protocol that utilizes a familiar melody (chosen specifically for the intended population) paired with a simple, at-home finger tapping exercise randomized controlled PD intervention group.Use fNIRS and motor control assessments at four time points collected throughout the study to assess how an external auditory stimulus (over time and repetition) coupled with motor movement affects motor synchronization and control in participants with PD. The collection time points are as follows: the first is collected after consent and allocation while the last 3 are sequentially collected 4-weeks apart from one another (i.e., 4 weeks, 8 weeks, and 12 weeks after the baseline measurement).Investigate the effects of music therapy in PD by comparing the neuronal activity changes and motor control performances between PD control arm and PD experimental group.

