### Trial design {8}

The study is a parallel two-group randomized controlled trial comparing motor timing performance of PD participants with and without music-based synchronous finger tapping training. In addition, data collected from a third arm, healthy controls, are assessed and serve as a normal, nonpathological baseline.

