#### Finger tapping performances and neuropsychological assessments

The SFT and CFT performances as well as neuropsychological measurements collected from the three groups (intervention and control arms) during assessment will be compared using a two-sample *t* test. Correlative data and the extent of the intervention’s effect on finger tapping performances and PD symptoms may be extrapolated from this data.

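### The tapping and HbO2 primary outcomes are worded as change within the intervention arm, at odds with the between-arm design, and 'preserved' has no margin for tapping, UPDRS, n-back and MoCA

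*Protocol article*

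**What the plan says.** **Outcome wording.** Outcomes {12} gives the tapping outcome as "Improvement or preservation of SFT and continuous finger tapping (CFT) performances from baseline measurements for intervention group". The HbO2 item asks for reduced "levels in prefrontal cortex from baseline measurements for intervention group". Neither names a comparator. In the same list, n-back and MoCA refer to "scores from baseline measurements for intervention group in comparison to control arm", and UPDRS is worded almost identically.

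**Preservation.** Tapping, UPDRS, n-back and MoCA are met by preservation or by improvement. HbO2 has to fall. The secondary outcome for PD controls begins "Preserved or aggravated motor control performances, UPDRS scores" and goes on to list the remaining measures.

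**Between-arm text.** Outcomes {12} adds that outcomes are determined from differences across visits in neuroimaging, neurophysiological and "SFT performance scores as well as compared with the data from the control arms". Objectives {7} includes "comparing the neuronal activity changes and motor control performances between PD control arm and PD experimental group". Trial design {8} states: "The study is a parallel two-group randomized controlled trial comparing motor timing performance of PD participants with and without music-based synchronous finger tapping training". Sample size {14} names HbO2 as the primary outcome and assumes a difference between the two PD groups. For tapping and the neuropsychological scores, data from the three groups "intervention and control arms) during assessment will be compared using a two-sample" t test.

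**HbO2 analysis.** The fNIRS data section allows contrast images to be averaged within groups and a group analysis by t test. It then has plotted group averages compared to judge the intervention effect. It does not say whether the t test is one-sample or two-sample, or which groups it contrasts.

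**The concern.** Randomisation protects only the comparison between the two PD arms. An outcome defined as change within the treated arm also picks up anything that moves both arms. Practice on the task is the obvious candidate: tapping is assessed four times in 12 weeks, and the motor-timing assessment section itself expects learning. If the HbO2 and tapping bullets were taken as the criteria for success, a shared shift could be reported as an effect of the music training.

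The preservation wording is a second, separate problem. Without a margin, preservation is met by no change, and the PD control wording also allows no change. A trial in which neither arm moves would therefore fit what is written for both arms. A test for a difference does not settle this, because a non-significant result is not evidence of preservation.

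**Working it through.** **1. The sections side by side**

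| Outcome | Comparator named in its bullet | No change fits the bullet | Test given in the methods |
|---|---|---|---|
| SFT/CFT tapping | No | Yes | Two-sample t test across three groups |
| Prefrontal HbO2 | No | No (must be reduced) | A t test; type and contrast not stated |
| UPDRS, n-back, MoCA | Yes, control arm | Yes, with no margin | Two-sample t test across three groups |

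For tapping, the bullet conflicts with the test. For HbO2, the bullet conflicts with the objective, design and power basis, and the test does not resolve it. The two wording problems coincide only for tapping.

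**2. The plan's own figure**

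Sample size {14} gives 70 per group with 10% attrition, α = 0.05 and 80% power (printed as β). No difference or SD is given, so 70 cannot be reproduced from the stated inputs. If a standardised difference of 0.5 is assumed, two-sided:

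- n = 2(1.960 + 0.842)² / 0.5² = 62.8, rounded up to 63 per arm
- 63 / 0.9 = 70

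Other assumed differences give other totals per arm after attrition: 0.4 gives 110, 0.45 gives 87, 0.55 gives 58 and 0.6 gives 49. So 70 per arm is compatible with a between-arm definition. With 63 evaluable per arm, the difference detectable with 80% power is 2.802 × √(2/63) = 0.50 SD.

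**3. Illustration: both arms shift equally, with no intervention effect**

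Assumptions: 63 evaluable (70 × 0.9), and a shared shift of s SDs of change in the favourable direction. The plan gives no such shift. A within-arm paired t test has 62 degrees of freedom, critical value 2.00 and noncentrality s√63 = 7.94s.

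| Assumed s | Noncentrality | P(within-arm test significant, favourable) |
|---|---|---|
| 0.1 | 0.79 | 0.12 |
| 0.2 | 1.59 | 0.35 |
| 0.3 | 2.38 | 0.65 |
| 0.4 | 3.17 | 0.88 |
| 0.5 | 3.97 | 0.97 |

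In the between-arm difference the shift cancels (s − s = 0). A two-sided 5% test therefore favours the intervention with probability 0.025 at every s.

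**4. Preservation when neither arm changes (s = 0)**

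- Read as mean change of at least zero: met with probability 0.50.
- Read as not significantly worse: met with probability 0.975.
- A favourable between-arm result at two-sided 5%: probability 0.025.

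If the treated arm truly declines by 0.25 SD (assumed), the paired test has 49.7% power to detect it. The not-significantly-worse reading would then still be met about 50% of the time.

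**The case against.** The best defence is that the trial plainly intends a comparison with control. The general sentence in Outcomes {12} covers every outcome, including tapping and HbO2. The objective, the design, the power basis and the tapping and neuropsychological t test are all between-arm. No paired within-arm test is planned anywhere. The trial calls itself exploratory, and the bullets can be read as expected directions, not decision rules. Three of the five outcomes name the control arm. For those, preservation against a worsening control arm is a real between-arm difference that a two-sample test can detect, and a shared practice effect cancels.

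Most of that stands. A reader might infer that the trial plans no control comparison, or that the 65% to 88% figure is its false-positive rate. The documents support neither: the comparison is planned, and the figure describes an analysis the protocol does not specify, under an assumed shift. A reader might also infer that no change in HbO2 counts as success; it does not, because HbO2 must be reduced.

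The defence does not remove the inconsistency. The general sentence sets the control comparison beside the across-visit differences without saying which one governs. For HbO2, the powered outcome, neither the definition nor the t test is tied to intervention versus PD control. A separate analysis plan may specify the test, but the outcome definitions printed here would still contradict it.

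**Conclusion.** The point holds as an unresolved inconsistency in the outcome definitions. Tapping and HbO2 are worded within-arm in a trial that is otherwise between-arm, and no rule says which comparison decides success. It matters most for HbO2, because that outcome carries the sample size. Separately, preservation without a margin leaves tapping, UPDRS, n-back and MoCA with wording that fits no change in either PD arm.

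The size is conditional. If success were judged by a within-arm test, a shared shift of 0.3 to 0.4 SD would produce a favourable result 65% to 88% of the time with no true effect, against 2.5% for the between-arm test. The shift and the use of a within-arm test are both assumptions. The wording conflict itself rests on no assumption.

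**What to change.** - In Outcomes {12}, restate tapping and prefrontal HbO2 as the intervention minus PD control difference in change from baseline at one prespecified visit. Week 8, the end of the intervention, is one candidate.
- In the fNIRS data section, state that the HbO2 group test is that two-sample comparison.
- For tapping, UPDRS, n-back and MoCA, drop preservation as a success criterion, or give it a margin and a matching non-inferiority analysis.
- Report within-arm changes, including those in PD controls, descriptively.

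The cost is a minor protocol amendment through the Steering Committee, Ethics Committee and Scientific Research Department, as the amendments section {25} requires. Success becomes harder to claim. The sample size need not change for the restated superiority outcomes; a preservation claim with a margin would need its own power check.
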